## Abstract

**Background:**

Urinary tract infections (UTI) are among the most prevalent microbial diseases and their financial burden on society is substantial. The continuing increase of antibiotic resistance worldwide is alarming. Thus, well-tolerated, highly effective therapeutic alternatives are urgently needed. Although there is evidence indicating that bacteriophage therapy may be effective and safe for treating UTIs, the number of investigated patients is low and there is a lack of randomized controlled trials.

**Methods and design:**

This study is the first randomized, placebo-controlled, double-blind trial investigating bacteriophages in UTI treatment. Patients planned for transurethral resection of the prostate are screened for UTIs and enrolled if in urine culture eligible microorganisms ≥10^4^ colony forming units/mL are found. Patients are randomized in a double-blind fashion to the 3 study treatment arms in a 1:1:1 ratio to receive either: a) bacteriophage (i.e. commercially available Pyo bacteriophage) solution, b) placebo solution, or c) antibiotic treatment according to the antibiotic sensitivity pattern. All treatments are intended for 7 days. No antibiotic prophylaxes will be given to the double-blinded treatment arms a) and b). As common practice, the Pyo bacteriophage cocktail is subjected to periodic adaptation cycles during the study. Urinalysis, urine culture, bladder and pain diary, and IPSS questionnaire will be completed prior to and at the end of treatment (i.e. after 7 days) or at withdrawal/drop out from the study. Patients with persistent UTIs will undergo antibiotic treatment according to antibiotic sensitivity pattern.

**Discussion:**

Based on the high lytic activity and the potential of resistance optimization by direct adaptation of bacteriophages, and considering the continuing increase of antibiotic resistance worldwide, bacteriophage therapy is a very promising treatment option for UTIs. Thus, our randomized controlled trial investigating bacteriophages for treating UTIs will provide essential insights into this potentially revolutionizing treatment option.

**Trial registration:**

This study has been registered at clinicaltrials.gov (www.clinicaltrials.gov/ct2/show/NCT03140085). April 27, 2017.

## Background

Urinary tract infections (UTI) are highly prevalent and put a substantial financial burden on the health care systems worldwide. In the USA alone, over 7 million physician consultations are due to UTIs [1], resulting in estimated direct and indirect costs of 1.6 billion US dollars [1]. Further, UTIs account for more than 100′000 hospital admissions annually [1], and for at least 40% of all hospital-acquired infections [2]. The increasing threat of antibiotic resistance, mainly due to uncritical use of antibiotics [3, 4], and the subsequent absence of access to effective antimicrobials constitutes a challenge for the future [5]. As UTIs account for approximately 15% of all community-prescribed antibiotics in the USA [6], they play an important role for direct antibiotic selection pressure. Thus, well-tolerated therapeutic alternatives to treat UTIs and to reduce antimicrobial resistances are highly warranted.

In 1917, d’Hérelle proposed the use of bacteriophages to treat bacterial infections. After a colorful episode, the discovery of penicillin by Alexander Fleming declined the interest for bacteriophages in the Western world rapidly [7]. At present, bacteriophage therapy is well accepted and registered in East European and post-Soviet countries like Georgia, Ukraine, Belarus, and Russia. Lately the use of bacteriophages as a target therapy against bacterial pathogens has gained a renewed interest. Reviews about several reports of successfully applied bacteriophage therapies for different medical specializations have been published [7, 8], and the role of bacteriophage as a possible treatment for difficult to treat microorganisms has been encountered [9–11]. A recent in vitro study could show excellent results (i.e. a high lytic activity) of commercially available bacteriophages for the most common bacterial strains found in UTIs [12]. Regarding UTIs, several current clinical studies showed positive effects of the use of bacteriophage therapy [10, 13–15]. Khawaldeh et al. reported on the success of adjunctive bacteriophage therapy after repeated failure of antibiotics alone [10]. An article in Russian language (http://www.bionow.ru/bnows-1020-2.html) describes successful treatments for topically applied (i.e. administrating bacteriophages into the urinary bladder) bacteriophages for several patients. However, well conducted clinical trials, a defined frame for bacteriophage therapy in the current Medicinal Product Regulation, and well-defined, safe bacteriophage preparations are still lacking. In consequence, the use of bacteriophage therapy is still not accepted as an official treatment against infectious diseases in the Western world [16, 17].

In line with recommendations of a multi-disciplinary expert panel on acceptance and re-implementation of bacteriophage therapy [11], we therefore designed a randomized, placebo-controlled, double-blind clinical trial to assess the efficacy and safety of intravesical bacteriophage treatment. We hypothesize that intravesical bacteriophage treatment in patients with UTIs due to *E. coli* and other uropathogens, shows a 40% increase in success rate (normalization of urine culture defined as no evidence of bacteria, i.e. <10^4^ colony forming units/mL) as compared to placebo treatment within 7 days. This difference is considered to be clinically relevant. We also hypothesize that bacteriophage treatment is non-inferior to antibiotic treatment in terms of treatment success rates, with a non-inferiority margin of 35%.

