### Determination of sample size

We are planning a study of independent cases and controls with 1 control per case. Superiority of bacteriophage versus placebo treatment: We assume the success rate among controls to be 0.2. If the true success rate for experimental subjects is 0.6, we will need to study 27 experimental and 27 control subjects to be able to reject the null hypothesis that the success rates for experimental and control subjects are equal with probability (power) 0.8. The type I error probability associated with this test of this null hypothesis is 0.05.

Non-inferiority of bacteriophage versus antibiotic treatment: We assume the success rate among subjects receiving bacteriophage treatment to be 0.6 and we accept a non-inferiority margin of 0.35. If the true success rate for experimental subjects is 0.95, we will need to study 27 experimental subjects and 27 control subjects to be able to remain within the non-inferiority margin with a probability (power) 0.8. The type I error probability associated with this test of this alternative hypothesis is 0.05. We will use a continuity-corrected chi-squared statistic or Fisher’s exact test to evaluate these hypotheses.

Thus, we will include 27 patients per treatment group, i.e. 81 patients in total. Withdrawn patients will be replaced.

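### Non-inferiority to antibiotic does not depend on superiority over placebo, so an agent no better than placebo could be declared non-inferior if the true antibiotic effect is under 35 points

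*Protocol article*

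**What the plan says.** The Background of the protocol article states two hypotheses. The first is that bacteriophage, against placebo, "shows a 40% increase in success rate". The second follows as an addition: "We also hypothesize that bacteriophage treatment is non-inferior to antibiotic treatment in terms of treatment success rates, with a non-inferiority margin of 35" (per cent).

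The section Determination of sample size treats them one after the other.

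- Superiority: "We assume the success rate among controls to be 0.2", and then "If the true success rate for experimental subjects is 0.6, we will need to study 27 experimental and 27 control subjects". The error rate is given as "The type I error probability associated with this test of this null hypothesis is 0.05".
- Non-inferiority: "We assume the success rate among subjects receiving bacteriophage treatment to be 0.6 and we accept a non-inferiority margin of 0.35", and then "If the true success rate for experimental subjects is 0.95, we will need to study 27 experimental subjects and 27 control subjects". The error rate is given as "The type I error probability associated with this test of this alternative hypothesis is 0.05".

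Neither section sets an order of testing, a condition linking the two claims, or a division of the 0.05. The margin is accepted without derivation from an antibiotic effect. No hypothesis compares antibiotic with placebo. Neither 0.05 is stated to be one-sided or two-sided.

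**The concern.** Being less than a margin worse than an active control means something only if it still implies benefit over no treatment. A 35-point margin guarantees that only where antibiotic beats placebo by more than 35 points. With placebo at the assumed 0.2, the boundary is an antibiotic rate of 0.2 + 0.35 = 0.55. Below it, an agent identical to placebo lies truly inside the margin.

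The trial already randomises the arm that guards against this. The non-inferiority hypothesis as written does not use it, so a report could claim non-inferiority to antibiotic beside a failed comparison with placebo. One of the trial's two main conclusions would then be uninterpretable.

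**Working it through.** **Inputs from the protocol article:** 27 per arm; placebo 0.2; bacteriophage 0.6; margin 0.35; 0.05 for each test; Fisher's exact test as one of the two named tests. The rate 0.95 is labelled as the experimental rate, but bacteriophage is already set at 0.6 in that calculation, so it is read here as the antibiotic rate.

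**Assumptions of this check:** non-inferiority is declared when the Newcombe lower limit for bacteriophage minus antibiotic lies above -0.35, at one-sided 0.05 or 0.025; superiority uses two-sided Fisher at 0.05; all rates other than 0.2, 0.6 and 0.95 are assumed.

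**1. The plan's own figure (superiority).**

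n = [1.96·√(2·0.4·0.6) + 0.8416·√(0.2·0.8 + 0.6·0.4)]² / 0.4² = (1.358 + 0.532)² / 0.16 ≈ 22.3.

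With continuity correction: (22.3/4)·[1 + √(1 + 4/(22.3·0.4))]² ≈ 27.1. That is 28 rounded up, within one of the stated 27. Exact enumeration of Fisher's test at 27 per arm gives power 0.802, so the stated 27 and 0.8 are reproduced.

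**2. Margin against the planned antibiotic effect.** The effect is 0.95 - 0.2 = 0.75, and 0.35/0.75 = 47%. At 0.2/0.6/0.95 (placebo/bacteriophage/antibiotic), P(non-inferiority without superiority) = 0.0002. With bacteriophage equal to placebo at 0.2 and antibiotic at 0.95, P(non-inferiority) is about 0.

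One reason for the 0.0002 is that non-inferiority is rarely declared at all at those rates (0.062 at one-sided 0.05), because the assumed difference, 0.95 - 0.60, equals the margin. That is a separate problem with the non-inferiority sample size.

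**3. Bacteriophage equal to placebo, other antibiotic effects.** With binomial counts X (bacteriophage) and A (antibiotic), each on 27 patients:

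P(non-inferiority) = Σ P(X = x)·P(A = a) over all pairs (x, a) whose lower limit exceeds -0.35.

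| Placebo = bacteriophage | Antibiotic | Antibiotic effect | P(non-inferiority), one-sided 0.05 | One-sided 0.025 |
|---|---|---|---|---|
| 0.20 | 0.40 | 0.20 | 39% | 29% |
| 0.20 | 0.50 | 0.30 | 14% | 9% |
| 0.20 | 0.60 | 0.40 | 3.0% | 1.5% |
| 0.20 | 0.70 | 0.50 | 0.3% | 0.1% |
| 0.20 | 0.95 | 0.75 | about 0 | about 0 |
| 0.70 | 0.95 | 0.25 | 30% | 19% |

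The last row keeps the planned 0.95 and changes only the placebo rate. With antibiotic at 0.95, the margin exceeds the antibiotic effect once placebo success is above 0.95 - 0.35 = 0.60.

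**4. The same scenarios with superiority required first.** P(superiority) by Fisher is 0.010 at 0.20 and 0.013 at 0.70, so no non-inferiority claim can be more frequent than that. The joint probability at one-sided 0.05 is 0.8% in the first row and 1.2% in the last.

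**5. A result the plan would allow.** Take bacteriophage 15/27, placebo 12/27, antibiotic 18/27. Superiority: Fisher p = 0.59. Non-inferiority: the difference is -0.111; with 90% Wilson limits 0.400 (lower, bacteriophage) and 0.795 (upper, antibiotic), the bound is -0.111 - √(0.155² + 0.128²) = -0.312. The 95% version gives -0.345. Both lie above -0.35, so non-inferiority would be declared. A simple Wald limit gives -0.328 and -0.369, so at one-sided 0.025 this example depends on the interval chosen.

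**6. Cost of the condition.** At bacteriophage 0.6, placebo 0.2, antibiotic 0.6 and one-sided 0.05, P(non-inferiority) is 0.89, and P(non-inferiority and superiority) is 0.75. With one-sided 0.025 as well, the joint probability is 0.71.

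**The case against.** The best defence is that the planning rates point elsewhere. Antibiotics are chosen by sensitivity pattern, the calculation uses 0.95, and at a 75-point effect the problem vanishes. This stands, and it limits the finding. A reader might infer that the margin exceeds the antibiotic effect the protocol plans for, or that an inert agent would probably be called non-inferior. The documents support neither; both need rates that the protocol does not assume. The reply is that 0.2 and 0.95 are stated as assumptions, all arms also undergo resection and have a suprapubic catheter, and a safeguard should not rely on the planning rates being right.

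A reader might also infer that the trial could not tell effective treatment from antibiotics that barely worked. That goes too far: the primary outcome is measured in all three arms, so antibiotic can be compared with placebo. What is missing is a rule that uses the comparison.

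Third, separate error rates in a sample-size section do not amount to a testing strategy, and an unseen analysis plan may add the condition. That is possible. The point rests on what this document does fix: two separately stated hypotheses, the margin, and 0.05 for each.

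Fourth, wherever the antibiotic effect is below 35 points, the true deficit is inside the margin, so declaring non-inferiority is not a type I error against that margin. This is correct. The harm is that the claim is empty, and the argument should not be put as inflated alpha. Two free tests at 0.05 could reach 0.10 in principle, but at 0.20/0.20/0.55, where both nulls hold, the chance of either claim is about 7.6%, nearly all from the non-inferiority test.

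Finally, setting the 35-point margin beside the 40-point difference called clinically relevant adds little, because that difference is against placebo.

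**Conclusion.** The concern holds as a conditional weakness. Nothing in the document makes the non-inferiority claim depend on benefit over placebo, and the margin does not ensure such benefit unless antibiotic beats placebo by more than 35 points. At the planning rates the consequence is negligible. With a 20- to 30-point antibiotic effect and bacteriophage equal to placebo, the chance of an empty claim is 14% to 39% at one-sided 0.05, or 9% to 29% at 0.025. It falls quickly once the effect exceeds the margin. These figures rest on assumed rates, a Newcombe bound, an assumed one-sided level, and 0.95 read as the antibiotic rate. This is a should-fix: the remedy is cheap and protects a main conclusion, but the planned scenario does not depend on it.

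**What to change.** State a fixed sequence in the protocol and analysis plan:

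1. Test bacteriophage against placebo for superiority at two-sided 0.05.
2. Claim non-inferiority to antibiotic only if step 1 succeeds.

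Report antibiotic against placebo with its confidence interval as a check of assay sensitivity. State the sidedness of the non-inferiority test and the interval method used to apply the margin.

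The sequence needs no extra patients and no division of alpha, and superiority power stays at 0.80. The price is that non-inferiority cannot be claimed when step 1 fails, as the 0.89 to 0.75 drop in the working shows. Moving the non-inferiority test to one-sided 0.025 is a separate choice that the sequence does not require. It lowers the 0.75 to 0.71, and at 0.6 against 0.6 it raises the required number per arm from 25 to 31, above the planned 27.

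### The 35-point non-inferiority margin equals the shortfall the plan assumes, so the stated 80% power is about 3% to 5% at the planned rates; separately, the margin is wide enough to pass a treatment with four times the antibiotic failures more often than not

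*Protocol article*

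**What the plan says.** The hypotheses at the end of the Background section set non-inferiority to antibiotics "with a non-inferiority margin of 35" (per cent). The section's one statement on clinical relevance, "This difference is considered to be clinically relevant", refers to the 40-point gain over placebo and not to the margin.

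Determination of sample size repeats the figure with the planning rate: "We assume the success rate among subjects receiving bacteriophage treatment to be 0.6 and we accept a non-inferiority margin of 0.35". It continues "If the true success rate for experimental subjects is 0.95", then states that "we will need to study 27 experimental subjects and 27 control subjects to be able to remain within the non-inferiority margin" with power 0.8. On the error rate it says only "The type I error probability associated with this test of this alternative hypothesis is 0.05"; whether the test is one-sided or two-sided is not given. The test named for both hypotheses is a continuity-corrected chi-squared or Fisher's exact test. The superiority calculation in the same section assumes 0.20 on placebo and also arrives at 27 per arm.

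**The concern.** A non-inferiority margin should be the largest loss against the comparator that would still be acceptable. Here it coincides with the loss the plan expects, and the text offers no other basis for it. Two things are at stake.

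- **Power.** If the true difference sits on the margin, the null hypothesis is true at its boundary, and the probability of rejecting it is about the type I error rate at any sample size. A stated power of 0.8 cannot then be right.
- **Meaning of a positive result.** With antibiotics at 0.95, a 35-point margin tolerates failures rising from 5% to just under 40%. A claim of non-inferiority on those terms could be read as similar efficacy when the treatment is clearly worse.

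**Working it through.** **Inputs** (Determination of sample size): bacteriophage 0.60; other group 0.95; placebo 0.20; margin 0.35; 27 per arm; power 0.80; alpha 0.05 with sidedness unstated, so each result is given at one-sided 0.025 / 0.05.

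**Which arm is 0.95?** The text labels it experimental, but bacteriophage is already set at 0.60. Taking the label literally (bacteriophage 0.95, antibiotic 0.60), the usual formula needs only 5 / 4 patients per arm, not 27. Only the antibiotic reading is coherent.

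**Step 1. Reproduce 27.** A two-sided test of equality of 0.95 and 0.60 has mean rate 0.775:

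n₀ = [1.960·√(2·0.775·0.225) + 0.842·√(0.95·0.05 + 0.60·0.40)]² / 0.35² = 21.1

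With continuity correction: n = (n₀/4)·[1 + √(1 + 4/(n₀·0.35))]² = 26.5, rounded up to 27.

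The stated number is therefore what a test of difference requires. The margin plays no part in it.

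**Step 2. Non-inferiority at the planned rates.**

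n = (z_α + z_β)²·[p_a(1 − p_a) + p_c(1 − p_c)] / [0.35 − (p_c − p_a)]²

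With p_c − p_a = 0.95 − 0.60 = 0.35 the denominator is zero, so no finite n exists. Power is Φ(0 − z_α), that is 2.5% / 5%. Exact enumeration of all 28 × 28 outcomes with a Miettinen-Nurminen score test gives 3% / 5%.

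**Step 3. Is there a reading that gives about 80%?** With equal true rates of 0.60, n = (z_α + z_β)²·0.48/0.1225, which is 31 / 25 per arm. So 27 roughly suffices at one-sided 0.05, but the stated 0.95 is then unused.

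**Step 4. Width.** 0.35 / (0.95 − 0.20) = 0.35 / 0.75 = 47% of the assumed antibiotic-placebo gap.

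**Step 5. Chance of declaring non-inferiority**, 27 per arm, same exact score-test enumeration, one-sided 0.025 / 0.05:

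| True rates, bacteriophage v antibiotic | Margin 0.35 | Margin 0.25 (illustration) |
|---|---|---|
| 0.60 v 0.95 (8 times the failures) | 3% / 5% | below 1% |
| 0.75 v 0.95 (5 times) | 34% / 46% | 6% / 13% |
| 0.80 v 0.95 (4 times) | 57% / 69% | 15% / 28% |
| 0.60 v 0.60 | 77% / 85% | 47% / 59% |
| 0.80 v 0.80 | 90% / 94% | 62% / 73% |
| 0.95 v 0.95 | over 99% | 90% / 97% |

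At 0.90 v 0.90, margin 0.25 has 77% / 88%.

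**Check by other methods.** With Wald and Newcombe bounds at margin 0.35, four times the failures passes 58–61% / 73% of the time, and five times passes 36–38% / 50%.

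**The case against.** The best defence is that the margin is declared openly: the plan says "we accept a non-inferiority margin of 0.35", so a reader knows what non-inferior means here, and a journal article may leave the rationale to the full protocol. That stands as far as the missing rationale goes. It does not rescue the power statement, which the article makes itself and which its own rates contradict.

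Four stronger readings are tempting, and the documents do not support them.

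- A reader might infer that the equality of margin and shortfall is what lets poor treatments pass. It is not. A treatment at the planned 0.60 passes only 3% / 5% of the time. The equality destroys the power; the width gives the false reassurance.
- A reader might set 35 points against the 40 points called clinically relevant. Those 40 points concern bacteriophage against placebo. The relevant yardstick is the comparator's assumed effect over placebo, of which the margin keeps just over half.
- A reader might conclude that a tighter margin costs nothing at this sample size. That is so only where power is already about alpha. At 0.60 v 0.60, moving to 0.25 lowers power from 77% / 85% to 47% / 59%.
- A reader might take 0.25 as the correct margin. Nothing in the documents gives it a clinical basis, and choosing it because 27 per arm can power it would again fit the margin to the sample size.

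It is also fair to say that at five times the failures the score-test pass rate stays below half. Moreover, all these rates presuppose a test against the margin. The chi-squared or Fisher test that the article names compares the arms for equality and does not test a margin. An analysis plan might replace it, but the article assigns it to this hypothesis.

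**Conclusion.** The point holds as two distinct faults. The power error is certain once 0.95 is read as the antibiotic rate: about 3% to 5% at the planned rates against a stated 80%, with no sample size that repairs it. The 27 per arm is the answer to a test of difference.

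The width problem is a matter of degree. At this margin a treatment with four times the antibiotic failures would be called non-inferior 57% / 69% of the time, and one with five times the failures 34% / 46%. These figures rest on an antibiotic rate of 0.95, 27 evaluable patients per arm and a score test against the margin. They show that the label would mislead without a justification. They do not show that 35 points is indefensible, nor which margin is right. The superiority comparison and the trial size are untouched.

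**What to change.** Keep 27 per arm, and make these changes in Determination of sample size and in the analysis wording:

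1. Analyse arm a minus arm c as a risk difference with a two-sided 95% confidence interval, and compare its lower limit with the margin, in place of the chi-squared or Fisher test of equality. This also settles the sidedness (one-sided 0.025).
2. Relabel 0.95 as the antibiotic rate, withdraw the 80% power at 0.60 v 0.95, and restate power at margin 0.35 under explicit true rates, using the equal-rate rows of the table.
3. Word a result that clears only −0.35 as not more than 35 percentage points worse than antibiotics. Reserve non-inferior for a margin that the sponsor justifies as an acceptable loss, and state its power at 27 per arm. The 0.25 column shows what such a choice would do and is not a recommendation.

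The cost is an amendment to wording and analysis, with no added patients. The downside is a less favourable stated power and a weaker claim; a tighter margin would also lower the chance of success if both true rates are well below 0.90.
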